## Methods/Design

### Setting and participants

The study will take place at one Federally Qualified Health Center that primarily serves a Hispanic population in north Texas and whose mission is to provide a community medical home through accessible, compassionate and quality health care services. The center offers a full range of quality family-oriented comprehensive primary and preventive services, including Family Medicine, Pediatrics, Obstetrics/Gynecology, family planning services, prenatal care, and health education promotion and disease prevention services. In 2013, the clinic had 11,274 unduplicated patients and 25,362 patient visits. Of those patients, 83 % were Hispanic. The majority did not speak English.

The target enrollment for recruitment is 350 patients over the 24-month study period. All adult primary care patients at the clinic will be asked to participate in screening for depression with the iPad Depression Screening application (universal screening). The clinic sees an average of 450–500 unique adult patients per month (new and/or unduplicated) or 100–125 patients per week. It is expected that *at least* 10 % of the patient population will screen positive for depression. Patients that are not Hispanic will be ineligible for the study because the intervention is culturally and linguistically adapted for a Hispanic population. Patients who are already in treatment for depression (medication and/or psychotherapy) will also be excluded since treatment engagement is an expected outcome. The study protocol was reviewed and approved by the Institutional Review Board of the University of Texas at Arlington. All patients will provide written informed consent to participate.

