In order to evaluate the secondary aim of feasibility of universal screening for depression utilizing the PHQ-9 [31] via the iPad Depression Screening application, a qualitative analysis will determine if the providers and other clinic staff are introducing the screening with practiced scripts and conducting warm handoffs to the Depression Educator after screening positive for depression. Additional analyses will quantify via the iPad and clinic records if all adult patients are being screened and the score is being placed in the EHR.

Other analyses of interest would determine if the iPad Depression Screening application results in changes in primary care provider approach to the diagnosis and treatment of depression. Such analyses would include comparing the number of Hispanic patients with new a depression diagnosis as a percentage of the total number of adult Hispanics patients seen in the clinic compared to a matched set the year prior to the study based on the EHR (baseline data). Additionally, quantifying changes in the number of patients with a depression diagnosis being treated with antidepressants by a primary care provider as a percentage of the total number of Hispanics patients seen in the clinic compared to a matched set the year prior to the study based on the EHR (baseline data).

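### The antidepressant indicator mixes detection with treatment, and its numerator and denominator describe different populations

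*Protocol article*

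**What the plan says.** The last paragraph of the Data monitoring and analysis section lists further analyses meant to show whether the screening application changes how primary care providers diagnose and treat depression. It names two indicators from the electronic health record (EHR).

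- **Diagnosis indicator:** "comparing the number of Hispanic patients with new a depression diagnosis", expressed "as a percentage of the total number of adult Hispanics patients seen in the clinic". Numerator and denominator are both Hispanic, and the denominator is adult.
- **Antidepressant indicator:** the change in the number of diagnosed patients "being treated with antidepressants by a primary care provider as a percentage of the total number of Hispanics patients seen in the clinic". The numerator does not say Hispanic, adult or new. The denominator says Hispanic but not adult, and it covers all patients seen, not those diagnosed.

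Both indicators are compared with a matched set from the year before the study.

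Three other statements bear on this. The Setting and participants section gives the clinic's 2013 patient mix: "Of those patients, 83 % were Hispanic". The same section lists Pediatrics among the services and says that all adult primary care patients, not only Hispanic ones, will be asked to take the screening. The Discussion expects the application to bring to light many cases of depression that had gone unrecognised.

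**The concern.** There are two faults, and the second matters more.

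1. **Populations.** As written, a non-Hispanic patient on an antidepressant counts in the numerator but can never be in the denominator. Children count in the denominator although only adults are screened. An EHR query built from this text would not match the one built for the diagnosis indicator.
2. **Two quantities in one.** Of the two named indicators, this is the only one that carries information on treatment. Because it divides by everyone seen, it moves with detection as well as with treatment, and detection is what the screening programme is designed to raise.

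At stake is the part of the provider hypothesis that says screening will improve the care the clinic gives. A rise in this indicator could be reported as a change in treatment practice when it reflects only more diagnoses, and it could hide a fall in the share of diagnosed patients who are treated.

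**Working it through.** The plan gives no value, expected change or sample size for this indicator, so there is no figure to reproduce. The checks below use the indicator's definition, the 83% Hispanic share from Setting and participants, and assumed rates that are labelled as such.

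**Step 1: what the indicator measures.** Let d be the share of patients seen who have a depression diagnosis, and t the share of those diagnosed who are treated with antidepressants. With numerator and denominator drawn from one population,

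treated / seen = (diagnosed / seen) × (treated / diagnosed) = d × t.

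The study-to-prior-year ratio is therefore (d1/d0) × (t1/t0). If detection doubles, the indicator rises unless t falls to half its earlier value or below.

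**Step 2: illustrations.** All values of d and t are assumed; the article gives none.

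| d, prior → study | t, prior → study | Indicator, prior → study | Ratio |
|---|---|---|---|
| 5% → 10% | 50% → 50% | 2.5% → 5.0% | 2.0 |
| 5% → 10% | 50% → 40% | 2.5% → 4.0% | 1.6 |
| 5% → 10% | 60% → 40% | 3.0% → 4.0% | 1.33 |
| 5% → 10% | 50% → 25% | 2.5% → 2.5% | 1.0 |
| 5% → 10% | 50% → 20% | 2.5% → 2.0% | 0.8 |
| 5% → 5% | 50% → 60% | 2.5% → 3.0% | 1.2 |

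In the second row treatment of diagnosed patients worsens and the indicator rises by 60%. In the last row treatment improves with detection unchanged and the indicator rises by only 20%. The size of the movement does not say which of the two happened. Treated-among-diagnosed shows it directly: 40% against 50% in the second row, 60% against 50% in the last.

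**Step 3: the population mismatch.** Let r be the treated rate in non-Hispanic patients divided by that in Hispanic patients (assumed). Counting everyone in the numerator over Hispanic patients only multiplies the level by 1 + r × 0.17/0.83:

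- r = 0.5: 1.10
- r = 1: 1.20
- r = 2: 1.41

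This factor cancels in a before/after ratio if the patient mix is stable. If the Hispanic share moved from 83% to 78% or to 88% (assumed, r = 1), the ratio would shift by 0.83/0.78 = 1.06 or 0.83/0.88 = 0.94, that is about 6% up or down, with no change in practice. The 83% is for all patients in 2013, not for adults, so these values are approximate.

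**The case against.** The strongest reply is that the stated purpose covers diagnosis and treatment together. Treated depression per patient seen is a legitimate population measure of that joint change, and the diagnosis indicator stands beside it, so a reader could see whether detection had risen. This stands in part. A reader might infer that the indicator cannot show any change in provider practice, and the documents do not support that. What it cannot do is isolate the treatment component. Setting the diagnosis indicator beside it does not allow a clean separation, because that one counts new diagnoses among adult Hispanic patients, while this one counts any diagnosis in a differently defined population.

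The missing word Hispanic in the numerator may be loose drafting, since the sentence continues one about Hispanic patients. That is plausible, but step 2 holds on either reading. It is also fair that children are excluded from neither part of this indicator, so the absence of an age limit does not by itself put the numerator outside the denominator. It does bring unscreened patients into a measure of screening.

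A reader might infer that 24 months of study data are set against 12 months. The article gives 24 months as the study and recruitment period and states no window for the study side of this comparison. The window is open, not wrong, and the matching could include equal length. Likewise, the article says too little about the matched set for it to be faulted.

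The article also plans to count diagnosed Hispanic patients who begin treatment after the education session, and by which modality. That count has no prior-year comparison, so it does not fill the gap.

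**Conclusion.** The point holds for this indicator, in two parts. Its numerator and denominator are not defined on the same population, which is a drafting error on the face of the text. Its denominator makes it the product of detection and treatment, so it rises with the detection that the study expects even when treatment of diagnosed patients is unchanged or falls.

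The second part is algebra and needs no assumption. Its size depends on rates the article does not give: under the assumed doubling of diagnosis, the ratio runs from 2.0 with treatment unchanged to 1.0 with the treated share halved. The first part is smaller. A reader might take the factor of 1.20 as bias in the comparison, but it affects the level and cancels if the patient mix is stable; the assumed five-point shifts in mix leave about 6%.

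The analysis is exploratory. No sample size rests on it, and the primary analysis of knowledge and stigma is untouched. It should be corrected because it bears on a stated hypothesis and the correction is cheap.

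**What to change.** Redefine the two indicators on one population, adult Hispanic patients seen in the clinic:

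1. New depression diagnoses divided by adult Hispanic patients seen.
2. Adult Hispanic patients with a new depression diagnosis who are treated with antidepressants by a primary care provider, divided by adult Hispanic patients with a new depression diagnosis. If any diagnosis is meant instead of a new one, say so and apply it to both parts.

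Treated patients per adult Hispanic patient seen can be kept as a labelled summary of the combined change. State that study and prior-year windows are of equal length. The matched comparison can stay.

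The cost is a rewording and a revised EHR query, with no new data. One caution should be written in: cases found by screening may differ in severity from those diagnosed the year before, which alone can move the treated-among-diagnosed share. The two indicators should therefore be read together.

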## Discussion

This study is unique in that it aims to examine the specific role of patient education as an intervention to increase engagement in depression treatment, as opposed to studies which provide patient education as a component of a larger depression treatment intervention. It is expected that the DEI will reduce barriers to treatment of depression for Hispanic patients by increasing knowledge of the disorder (disease literacy), its causes, symptoms and its role in chronic disease. Discussion of myths related to treatment will help allay fears of engaging in treatment. By participating in the DEI, it is expected that patients will have time to understand treatment options, participate in shared decision making with their provider about treatment, and increase engagement in treatment of depression which will lead to improved overall health.

While it is expected that implementation of the iPad Depression Screening application will increase identification of a large number of patients whose depression was previously unrecognized and might increase the workload of the primary care providers, with the support of the DEI, the burden of patient education about the disease and its treatment options will be reduced. Additionally, the recognition and treatment of depression will improve the treatment of comorbid chronic disease and ultimately reduce the burden on the primary care practice.

## Abbreviations

CMS, Center for Medicare and Medicaid Services; DEI, Depression Education Intervention; DESEO, Depression Screening and Education: Options to Reduce Barriers to Treatment; DKM, Depression Knowledge Measure; D-Lit, Depression Literacy questionnaire; DSM-IV, Diagnostic and Statistical Manual of Mental Disorders; EHR, electronic health record; LSAS, Latino Scale for Antidepressant Stigma; MDDC, major depression diagnostic checklist; PHQ-2, first two screening items of the PHQ-9; PHQ-9, 9-item Patient Health Questionnaire; SCMHC, Stigma Concerns about Mental Health Care; SD, Social Distance scale
